### Intervention

The weighted blankets are fibre blankets (Novista.se) which distribute the weight evenly across the body, in comparison with other weighted blankets, such as ball blankets [38] or chain blankets [39], where the pressure is concentrated on certain points on the body [38, 39]. Children included in the research project receive a weighted blanket (4 kg, 6 kg, 8 kg, or 10 kg) with weight based on age, body weight, and degree of sleep problems, according to a specifically designed manual that follows practice for prescribing blankets. Melatonin will start at 1 or 2 mg, with a dose range up to 6 mg.

### Data collection and assessment

The child-parent dyads answer individual questionnaires at baseline (before the intervention starts), at 1-, 3-, and 6-month follow-ups, at 1-year follow-up, and then annually for an additional nine years. Parent-reported measures include both parent self-reports and parent proxy-reports concerning the child. The questionnaires contain questions about sleep problems, everyday function, lifestyle habits, worry and anxiety, ADHD-related symptoms, health-related quality of life, pain, resource utilization, and questions related to the intervention (Table 1). A purposive sample of approximately 20–25 child-parent dyads from each treatment arm will be interviewed individually at 6 and 12 months.

The implementation of the intervention will be evaluated by resource utilization and interviews. Approximately 5–10 individuals from the clinical staff at the ADHD unit will be interviewed individually and/or in focus groups at 6 and 12 months.

**Table 1 Tab1:** Overview of outcome measures

		Child-reported measures	Parent-reported measures	Clinical staff–reported measures
**Sociodemographic variables**			Children: age, gender, country of birth, medical information, siblings, and age of siblings *. Parents: age, gender, country of birth, civil status, educational level, and employment. Partners: age, country of birth, educational level, and employment.	
**Primary outcomes**	Sleep problems		Children’s Sleep Habits Questionnaire (CSHQ) [36, 37] *, **	
	Treatment adherence and treatment changes		Usage of weighted blanket and/or melatonin *	
**Additional sleep-related measures**	Sleep problems	Insomnia Severity Index (ISI) [40] Sleep Self-Report (SSR) [41, 42]	Pediatric Insomnia Severity Index (PISI) [43] *	
**Secondary outcomes**	Everyday function	Child Outcome Rating Scale (CORS) [44] Work and Social Adjustment Scale, Youth version (WSAS-Y) [45]	Outcome Rating Scale (ORS) [46] Work and Social Adjustment Scale, parent version (WSAS-P) [45] * The Brief Child and Family Phone Interview (BCFPI) [47, 48] *	
	Lifestyle habits		Dietary habits, physical activity, screen time and sedentary time (Health Behaviour in School-aged Children (HBSC) survey) [49] *	
	Worry and anxiety	The State-Trait Anxiety Inventory – short form (Short STAI) [50–52]		
	ADHD-related symptoms		The Swanson, Nolan, and Pelham Scale (SNAP-IV parent) [53, 54] *	
	Health-related quality of life	EQ-5D-Y-3 L [55, 56]	EQ-5D-3 L [57, 58]	
	Pain	Visual Analogue Scale (VAS) [59]		
	Resource utilization		Treatment Inventory Cost in Psychiatric Patients (TIC-P) [59] School absence and healthcare consumption [60, 61] *	Healthcare consumption Costs of implementation
	Evaluation of intervention implementation			Checklist: Extent of implementation, accessibility and participant recruitment
	Interviews	Individual interviews regarding the sleep intervention: 1) Experiences of the interventions’ effects 2) Barriers and facilitators in the implementation process	Individual interviews regarding the sleep intervention: 1) Experiences of the interventions’ effects 2) Barriers and facilitators in the implementation process	Individual and/or focus group interviews on barriers and facilitators in the implementation of the sleep intervention

* Parent proxy-report concerning the child

** Primary sleep outcome for the main effectiveness evaluation

#### Sociodemographic variables

Parents will be asked to report their gender (man/woman/prefer not to say), child’s gender (boy/girl/prefer not to say), age, child’s age, civil status (single/spouse or partner), partner age, birth country, birth country of child, birth country of partner, highest educational level achieved (compulsory school/upper secondary school/university or college), partner’s highest educational level achieved, employment status (full time/part time/unemployment/parental leave/studies/sick leave or sickness benefit/other), partner’s employment status, number of siblings, and sibling(s’) age(s). Parents also report child comorbidity (no/yes and diagnoses), child medication (no/yes and type of medicines), child’s need for sleep medication (no/yes), and completion of treatment for sleep problems for the child during the last month (no/yes and type of treatment). An open-ended question enabling additional important information to be communicated is also included.

#### Primary outcomes

In relation to the main evaluation of real-world effectiveness, two main outcome areas will be studied: sleep problems and treatment adherence. The primary sleep outcome will be parent-reported sleep problems assessed by the Children’s Sleep Habits Questionnaire (CSHQ) total score. Treatment adherence and treatment changes over time will be assessed by studying continued use, discontinuation, switching between weighted blanket and melatonin treatment, combined treatment use, and withdrawal from the study.

##### Sleep problems

###### Children’s sleep habits questionnaire (CSHQ)

The Children’s Sleep Habits Questionnaire (CSHQ) [37], Swedish version (CSHQ-SWE) [36] is a parent-reported questionnaire assessing sleep during the past week in children by 33 questions. The frequency of sleep problems (questions 1–31) or sleepiness during various activities (questions 32–33) for each question is answered on a three-point scale (1–3 points). The questions are divided into eight dimensions: (1) Bedtime resistance, (2) Sleep onset delay, (3) Sleep duration, (4) Sleep anxiety, (5) Night wakings, (6) Parasomnias, (7) Sleep-disordered breathing, and (8) Daytime sleepiness. In addition to dimensions, the severity of sleep problems is summed into a total score (range 33–99), where a higher score indicates a greater degree of sleep problems [37]. The clinical cut-off for sleep problems in school-aged children with ADHD is 48 [40]. Non-scored inquiries encompass the child’s bedtime, the time the child fell asleep, the duration of night sleep and naps, the number and duration of night wakings, and the time of morning awakening [36]. The questionnaire was originally validated in 4–10 year-old children [37], but has been used in children up to 12 years of age [41]. The Swedish version is validated for use in children with ADHD aged 6–12 [36].

##### Treatment adherence

Treatment adherence and treatment changes over time will be assessed by studying continued use, discontinuation, switching between weighted blanket and melatonin treatment, combined treatment use, and withdrawal from the study.

#### Additional sleep-related measures

Additional sleep-related measures will be used to capture different aspects of sleep and to include both parent proxy-reported and child self-reported perspectives across the broad age range and follow-up period.

##### Sleep problems

###### Insomnia severity index (ISI)

The Insomnia Severity Index (ISI) [42] assesses insomnia in the past two weeks by seven questions. The first questions encompass difficulties with: (1) Sleep onset, (2) Sleep maintenance, and (3) Early morning awakening. The remaining questions concern: (4) Satisfaction with current sleep pattern, (5) Interference with daily functioning, (6) Noticeability of impairment attributed to the sleep problem, and (7) Level of distress caused by the sleep problem. A version will be used that has been adapted specifically for children. The children rate the severity of sleep problems on a five-point scale (0–4), which is summed to a total score (0–28), with higher scores indicating greater sleep problems [42].

###### Pediatric insomnia severity index (PISI)

The Pediatric Insomnia Severity Index (PISI) [43, 44] is a parent-reported questionnaire assessing insomnia during the past week in children by six questions, encompassing difficulties with: (1) Sleep onset delay, (2) Sleep onset, (3) Nightly awakenings, (4) Falling back to sleep after nightly awakenings, (5) Daytime sleepiness, and (6) Sleep duration. The parents rate the frequency of sleep problems on a six-point scale (0–5 points), and the severity of sleep problems is summed into a total score (range 0–30 points), where a higher score indicates a greater degree of sleep problems. PISI is validated in 4–10-year-olds [43, 44], but has also been used in parents with children aged 10–12 [45].

###### Sleep self-report (SSR)

The Sleep Self-Report (SSR) [46, 47] is a child-reported questionnaire that assesses frequency of sleep-related difficulties with a focus on bedtime, sleep behavior and daytime sleepiness. The SSR contains 26 questions, of which 23 are answered on a three-point scale (1–3 points), and the remaining three are non-scored inquiries. The total score ranges from 23 to 69, with a higher score indicating more sleep problems [46]. The questionnaire was originally validated in 7–12-year-olds [46], but has also been used up to the age of 18 [48, 49]. SSR shows sufficient sensitivity to distinguish a clinical population from a general population [50].

#### Secondary outcomes

##### Everyday function

###### Child outcome rating scale (CORS)

The Child Outcome Rating Scale (CORS) [51] assesses everyday function and well-being in the domains of individual, family, school, and overall. Each domain is rated by the child on visual analogue scales (VAS) ranging from 0 (frowning face) − 10 (happy face), where 10 corresponds to the best. In addition, a total score ranging from 0 to 40 (worst–best) will be utilized. CORS demonstrates satisfactory validity and reliability [51].

###### Outcome rating scale (ORS)

The Outcome Rating Scale (ORS) [52] assesses parents’ everyday function and well-being in the domains of individual, interpersonal, social role, and overall. Each domain is rated by the parent on VAS, ranging from 0 to 10, where 10 corresponds to the best. In addition, a total score ranging from 0 to 40 (worst–best) will be utilized. ORS demonstrates satisfactory validity and reliability [52].

###### Work and social adjustment scale, youth version (WSAS-Y)

The Work and Social Adjustment Scale, Youth version (WSAS-Y) [53] assesses children’s daily functioning. The instrument consists of five questions where children estimate on a nine-point scale (0–8 points) the extent to which their problems affect school, daily skills, social activities, hobbies, and family and relationships. A total score ranging from 0 to 40 is obtained, with higher scores indicating greater adverse impact. WSAS-Y demonstrates satisfactory validity and reliability [53]. A version specifically adapted to children with ADHD will be used.

###### Work and social adjustment scale, parent version (WSAS-P)

The Work and Social Adjustment Scale, Parent version (WSAS-P) [53] assesses children’s daily functioning. The instrument consists of five questions where parents estimate on a nine-point scale (0–8 points) the extent to which the children’s problems affect school, daily skills, social activities, hobbies, and family and relationships. A total score ranging from 0 to 40 is obtained, with higher scores indicating greater adverse impact. WSAS-P demonstrates satisfactory validity and reliability [53]. A version specifically adapted to parents assessing children with ADHD will be used.

###### The brief child and family phone interview (BCFPI)

The Brief Child and Family Phone Interview (BCFPI) [54, 55] is a screening tool consisting of scales for DSM-related symptoms that is used in CAMHS to triage mental health conditions in children. Selected scales will be utilized: “Impact on child functioning” (social participation, quality of social relations, and school participation and achievement), “Impact on family functioning” (family activities and family comfort), and “Parental functioning” (appetite problems, concentration problems, and emotional problems). The frequency of each event is rated by the parents on Likert scales (best–worst). BCFPI demonstrates satisfactory validity and reliability [54, 55].

##### Lifestyle habits

###### Lifestyle habits

The child’s lifestyle habits will be estimated by parents by selected questions included in the Health Behaviour in School-aged Children (HBSC) survey carried out by the Public Health Agency of Sweden [56]. The child’s height and weight, dietary habits (fruit intake, vegetable intake, consumption of sweets, and consumption of sugar-sweetened beverages), physical activity (fulfillment of recommendations, frequency of and time spent on exercise during leisure time) and screen time and sedentary (time spent in front of screen-based entertainment, time spent in sedentary gaming, and time spent using electronic devices for other purposes) are assessed [56].

##### Worry and anxiety

###### The state-trait anxiety inventory scale – short form (Short STAI)

The State-Trait Anxiety Inventory Scale – short form (Short STAI) [57, 58, 62] assesses anxiety in children by six questions encompassing the themes of Calm, Tense, Upset, Relaxed, Content, and Worried. Each question is rated by the child on a four-point Likert scale (1–4 points), and the total score ranges from 6 to 24 points with higher scores indicating more anxiety [57, 58]. Short STAI demonstrates satisfactory validity and reliability [57, 58].

##### ADHD-related symptoms

###### The swanson, nolan, and pelham scale – parent-reported version (SNAP-IV parent)

The Swanson, Nolan, and Pelham Scale – parent-reported version (SNAP-IV parent) [59, 60] assesses children’s ADHD symptoms and Oppositional Defiant Disorder (ODD) symptoms. The questionnaire includes 30 questions rated by the parent on a four-point Likert scale (0–3 points). Attention deficit is covered by nine items and scored from 0 to 27 points. Hyperactivity and impulsivity are combined, covered by six items and three items respectively, and scored from 0 to 27 points. ODD is covered by eight items and scored from 0 to 24 points. A higher score reflects greater severity of symptoms. The additional four items are supplementary to ADHD (two items) and ODD (two items) and will not be included in scoring [59, 60]. SNAP-IV parent demonstrates satisfactory validity and reliability [59, 61].

##### Health-related quality of life

###### EQ-5D-Y-3L

The EQ-5D-Y-3L [63, 64] is a child-reported measure that assesses health-related quality of life in children. The questionnaire covers five domains: mobility, looking after myself, doing usual activities, having pain or discomfort, and feeling worried, sad or unhappy. Problems within each domain are rated by the child on a three-point Likert scale (1–3 points) and re-calculated into an index ranging from 0.00 to 1.00 (worst–best). The questionnaire also includes a VAS (0–100 points, worst–best) to reflect current health state [63, 64]. EQ-5D-Y-3L demonstrates satisfactory validity and reliability [64].

###### EQ-5D-3L

The EQ-5D-3L [65–67] assesses health-related quality of life in adults. The questionnaire covers five domains: mobility, self-care, usual activities, pain/discomfort, and anxiety/depression. Each domain is rated by the parent on a three-point Likert scale (1–3 points) and re-calculated into an index ranging from 0.00 to 1.00 (worst–best). The questionnaire also includes a VAS (0.00–100.00 points, worst–best), reflecting current health state [65–67]. EQ-5D-3L demonstrates satisfactory validity and reliability [67–69].

##### Pain

###### Pain

Pain intensity during the last week is assessed by a VAS. The child estimates their perceived pain intensity on a scale from 0 to 100, where 0 corresponds to “no pain” and 100 corresponds to “worst pain possible”. VAS has been recommended for assessment of chronic pain in children [70].

##### Resource utilization

###### Treatment inventory cost in psychiatric patients (TIC-P)

The Treatment Inventory Cost in Psychiatric Patients (TIC-P) [71] is a questionnaire that assesses absence from work and changes in work productivity for parents. Six selected items covering those aspects will be utilized. TIC-P demonstrates satisfactory validity and reliability [71].

###### School absence and healthcare consumption

Absence from school and healthcare consumption for the children, such as number of visits to medical doctors, nurses, psychologists, emergency departments and specialist care providers, will be reported by parents. The questions have been used in previous studies [72, 73]. Healthcare consumption also includes clinical registry data from the medical health records of the participating children, including the number of visits to the CAMHS and the ADHD unit, type of visit, healthcare professional involved, and prescribed pharmacological treatment.

###### Costs of implementation

Costs of implementation include the costs of prescription of weighted blankets or melatonin, the healthcare region’s purchase price of weighted blankets or melatonin, administrative costs, and clinical staff time.

##### Evaluation of intervention implementation

###### Usage of weighted blanket and/or melatonin

Parents will report frequency of usage of weighted blanket and/or melatonin on a 4-point scale (every night = 6–7 nights a week; almost every night = 4–5 nights a week; sometimes = 2–3 nights a week; almost never = 0–1 night a week). An additional three open-ended questions will be available concerning how weighted blankets and/or melatonin have been used, the reason for usage, and thoughts about usage.

###### Checklist

A checklist will be maintained by clinical staff and researchers in the project to evaluate the extent of implementation, accessibility and recruitment of participants, and treatment use over time, including continued use, discontinuation, switching between treatments, combined use of weighted blankets and melatonin, and withdrawal from the study.

##### Interviews

###### Interviews with children and parents

Individual interviews will address the effects of the intervention (weighted blanket or standard treatment with melatonin) and how sleep affects the child’s everyday functioning, everyday activities, worry and anxiety, ADHD-related symptom burden, health-related quality of life, sensory impressions, and parents’ health, and will include questions about the implementation of the intervention and participation in the research project. Probing questions will be used to elicit in-depth responses.

###### Interviews with clinical staff

Individual interviews and/or focus group interviews will be carried out at the ADHD unit with multi-disciplinary clinical staff, addressing the barriers and facilitating factors in the process of implementing the sleep intervention in clinical practice, resources, and strategies utilized. Probing questions will be used to elicit in-depth responses.

### Statistical power

The primary outcome is the CSHQ total score. In the absence of an established minimal clinically important difference for the CSHQ and robust estimates of the expected effect of melatonin on CSHQ scores, the sample size calculation was based on previous publications from the SLEEP project, including the randomized controlled crossover trial and subsequent analyses of the same cohort [27, 74, 75], together with studies of melatonin interventions using the CSHQ [76, 77]. In the SLEEP project, the baseline mean CSHQ total score was approximately 53, with an SD of approximately 8, and an assumed follow-up mean of 47 was used for the weighted blanket intervention. Studies of melatonin interventions have reported improvements of approximately 10 points, corresponding to an assumed follow-up mean of 43, with an SD of 8 [76, 77]. Based on the assumed follow-up means of 47 and 43 and a common SD of 8, the standardized effect size was estimated as Cohen’s d = (47 − 43)/8 = 0.50. With 80% statistical power and a two-sided alpha of 0.05, 64 participants are required per treatment group. Given the uncertainty in the assumptions underlying the sample size calculation, and to allow for expected attrition, switching between treatments, combined use of weighted blankets and melatonin during the first 12 months, and retention of a sufficient sample for longer-term follow-up analyses, we aim to include 150 children per initial treatment arm, for a total of 300 children.

### Data analysis

#### Quantitative methods

Data analysis will be performed using IBM SPSS Statistics software v.28 or later (IBM Corp., Armonk, NY, USA). Continuous data will be presented as means and standard deviations or medians and interquartile ranges, and categorical data as numbers and percentages. Changes over time in continuous outcomes assessed repeatedly, including the primary sleep outcome, additional sleep-related measures, and health-related outcomes, will be analyzed using repeated-measures analysis of variance (R-ANOVA) or repeated-measures analysis of covariance (R-ANCOVA), as appropriate. Analyses to assess real-world effectiveness within and across the initial treatment arms will include the primary sleep outcome, treatment adherence, health-related outcomes, and resource utilization, using appropriate statistical methods, such as t-tests, chi-squared tests, or analysis of covariance (ANCOVA). When appropriate, age, sex, ADHD medication, and level of ADHD symptoms, will be included as covariates in R-ANCOVA or ANCOVA models. Analyses of long-term follow-up will take into account patterns of treatment use and changes over time, including continued use, discontinuation, switching between treatments, and combined use of weighted blankets and melatonin. Differences in resource utilization will be analyzed through non-parametric analyses of individual data. To address the risk of Type I errors due to multiple comparisons across several outcome measures, Bonferroni corrections will be applied where appropriate.

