## Discussion

Weighted blankets have demonstrated potential to reduce perceived sleep problems [27, 29, 30]; however, to the best of our knowledge, no study has previously explored the process of implementing a weighted blanket intervention in clinical practice for children with ADHD and sleep problems. There is also a knowledge gap concerning real-world effectiveness, longer-term patterns of treatment use, adherence, and treatment changes, and implementation of a weighted blanket intervention and standard melatonin treatment in routine clinical practice. This research project will address these gaps by following sleep-related outcomes, treatment adherence, health-related outcomes, resource utilization, and treatment changes, including continued use, discontinuation, switching between treatments, and combined use of weighted blankets and melatonin, within and across the initial treatment arms over time. The results will inform future evaluation of treatment options for children with ADHD and sleep problems and support the implementation of weighted blanket interventions in clinical practice. Moreover, the assessment of various aspects of the health of children and their parents will add to knowledge on how the child’s ADHD diagnosis combined with sleep problems affects the family in their everyday lives.

Methodological considerations need to be discussed. A strength of the research project is that it includes both questionnaires and interviews. The questionnaires capture diverse and broad outcomes and will be answered by both children and parents. Moreover, the multi-informant design of interviews ensures that children’s, parents’ and clinicians’ perspectives are taken into consideration, strengthening the generalizability and applicability in clinical settings and everyday life. The use of quantitative, qualitative, and mixed methods ensures rich data, which could support validity of results.

A methodological challenge is to ensure participation in the longitudinal follow-ups. The battery of questionnaires is extensive, and follow-ups are frequent during the first year, which may reduce participants’ willingness to continue participating. To address this, each parent will be contacted by the research team at recruitment by phone so questions can be answered, aims revisited, and the importance of adherence can be emphasized.

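### Repeated-measures ANOVA/ANCOVA for change in the CSHQ score drops every child who misses one modelled visit, although the plan expects missed visits; a mixed model would keep them

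*Protocol article*

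**What the plan says.** The Statistical power section states: "The primary outcome is the CSHQ total score". Under Data collection and assessment, questionnaires are due at baseline, then "at 1-, 3-, and 6-month follow-ups, at 1-year follow-up, and then annually for an additional nine years". Study design limits the main evaluation to the first 12 months and calls the annual phase exploratory, so the main evaluation has five waves: baseline and four follow-ups.

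For changes over time in repeated continuous outcomes, with the primary sleep outcome named among them, Quantitative methods says they "will be analyzed using repeated-measures analysis of variance (R-ANOVA) or repeated-measures analysis of covariance (R-ANCOVA), as appropriate". The next sentence of that section lists t-tests, chi-squared tests or ANCOVA as examples of methods for effectiveness within and across the initial arms, again including the primary sleep outcome.

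The protocol anticipates incomplete follow-up in two places. Statistical power enlarges the sample "to allow for expected attrition, switching between treatments, combined use of weighted blankets and melatonin during the first 12 months", among other reasons. The Discussion concedes: "The battery of questionnaires is extensive, and follow-ups are frequent during the first year", and adds that this may make families less willing to continue. Neither place gives a rate.

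**The concern.** Standard repeated-measures ANOVA or ANCOVA needs a complete row of outcome values for each child. A child with four of five CSHQ scores contributes nothing, even though those four scores carry most of the information about that child's course. The plan thus pairs a complete-case method with a schedule that its authors expect some families not to complete.

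Two things are at stake. The first is precision, because partial records are discarded without need. The second is representativeness: the results would describe families who returned every CSHQ form in the model. If earlier scores influence who drops out, and do so differently in two arms chosen by family preference, the complete-case difference can be biased.

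**Working it through.** **Inputs from the protocol.** 150 children per arm; assumed follow-up means 47 and 43; SD 8; 80% power; two-sided alpha 0.05; 64 required per group (all from Statistical power); four follow-ups to 12 months (Data collection and assessment).

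**Assumptions, because the documents give no figure.** A share m of children misses each follow-up, independently across visits, with m from 5% to 20%. Baseline is always observed. All pairs of visits correlate 0.6 (compound symmetry).

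**Step 1: the plan's own figure.** d = (47 − 43)/8 = 0.50. The normal approximation gives n = 2 × (1.960 + 0.842)² / 0.50² = 62.8, so 63. The t-based solution is 63.77, so 64, with power 80.1%. The stated 64 is reproduced.

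**Step 2: complete cases.** n_c = 150 × (1 − m)⁴. For m = 10%: 150 × 0.6561 = 98.4.

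**Step 3: variance of the 12-month arm difference in change.** The variance of one child's change is 2 × 8² × (1 − 0.6) = 51.2.
- Complete cases: 2 × 51.2 / n_c. At 10% this is 102.4 / 98.4 = 1.040.
- All children with a 12-month value: 102.4 / [150 × (1 − m)]. At 10% this is 102.4 / 135 = 0.759.
- Likelihood-based estimate: sum the information on the five visit means over the 16 possible patterns of missed follow-ups, each weighted by its probability, invert, and apply the contrast (12 months minus baseline). At 10% this gives 0.729.

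| Missed per follow-up | Complete cases per arm (share of 150) | Complete-case / likelihood variance | 12-month available / likelihood variance |
|---|---|---|---|
| 5% | 122 (81%) | 0.838/0.705 = 1.19 | 0.719/0.705 = 1.02 |
| 10% | 98 (66%) | 1.040/0.729 = 1.43 | 0.759/0.729 = 1.04 |
| 15% | 78 (52%) | 1.308/0.758 = 1.73 | 0.803/0.758 = 1.06 |
| 20% | 61 (41%) | 1.667/0.790 = 2.11 | 0.853/0.790 = 1.08 |

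**Step 4: when would complete cases fall below 64?** Solving 150 × (1 − m)⁴ = 64 gives m = 1 − (64/150)^¼ = 19.2% per follow-up. If children only leave for good, 12-month attrition must exceed 1 − 64/150 = 57.3%; attrition of 30% leaves 105. As a mixed example, 20% permanent drop-out plus 15% occasional misses per visit leaves 150 × 0.80 × 0.85⁴ = 63 complete cases, against 150 × 0.80 × 0.85 = 102 children with a 12-month value.

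**Step 5: bias.** In simulations where drop-out in the blanket arm depended on the previous CSHQ score, complete cases gave 4.08 to 4.36 against a true difference of 4.00, depending on the strength of the dependence. The likelihood estimate stayed at 3.97 to 3.99. The largest error, 0.36 points, is 0.36/8 = 0.045 SD. That missingness was at random by construction, so the example illustrates the mechanism and does not predict the bias in this study.

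**The case against.** The strongest counter-argument is that R-ANOVA is not the only method the plan names for the CSHQ. The section also offers t-tests or ANCOVA for effectiveness within and across arms, and these need only the visit analysed, plus baseline for ANCOVA. By the last column of the table, a 12-month change comparison in all children with that visit loses only 4 to 8% in variance at 10 to 20% missing. This stands, and it confines the point to the change-over-time analysis. It does not remove it: that analysis covers the primary outcome, and running both methods would put different children into two sets of results for one score.

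A reader might infer that missed visits will take the study below the 64 per arm it needs. The documents do not support that:
- No missing rate is given, and the break-even of about 19% per follow-up is an assumption-driven figure.
- The protocol says "we aim to include 150 children per initial treatment arm, for a total of 300 children", which is 150/64 = 2.3 times the requirement, partly to absorb attrition.
- The 64 belongs to a two-group comparison of means at one follow-up and takes no credit for correlation with baseline. With 61 per arm and a difference of 4, power is 78% for that plain comparison, but 86% for a change score and 93% for baseline-adjusted ANCOVA at correlation 0.6.

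Nor does the method require every questionnaire. Deletion applies to the outcome and waves in a given model, which is five waves in the main evaluation.

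Finally, this is a condensed article. An analysis plan may add missing-data handling, such as imputation before R-ANOVA, or name the primary visit. Silence on those is no finding here. The choice of R-ANOVA/R-ANCOVA, however, is stated in this document.

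**Conclusion.** The point holds as a criticism of the method chosen for change over time. Complete-case repeated-measures ANOVA/ANCOVA wastes partial follow-up that the plan expects to occur. At an assumed 5 to 20% missed per follow-up it discards 19 to 59% of each arm, and the variance of the 12-month difference in change is about 1.2 to 2.1 times that of a likelihood-based estimate. These figures rest on independent misses, complete baselines, SD 8 and equal correlation 0.6. Less scattered missingness, such as permanent drop-out only, would cost less. Bias is possible but its size cannot be given from the documents.

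This is a worthwhile improvement to the analysis of the primary outcome. It is not evidence that the study is too small, and the arm comparison would lose far less if done by the t-test or ANCOVA also listed.

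**What to change.** Replace R-ANOVA/R-ANCOVA, for the CSHQ total score and the other repeated continuous outcomes, with a linear mixed model for repeated measures in SPSS, fitted to all available visits. Include visit as a categorical factor, arm, arm × visit, the baseline score and the covariates already listed (age, sex, ADHD medication, level of ADHD symptoms), with an unstructured covariance. Take the arm comparison from the same model as the adjusted difference at 12 months. Keep complete-case R-ANOVA as a sensitivity analysis.

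The cost is a change of wording and slightly more work to fit and report; no new data are needed. The model's validity still rests on a missing-at-random assumption, so it does not protect against drop-out that depends on unobserved scores. It also does not by itself resolve confounding from the non-randomised choice of arm.
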